### Safety and indemnity

The major risk of endovascular treatment is dislodgement and distal embolisation of plaque and thrombotic debris, which may lead to stroke. In a recent review of reports on 331 endovascular treatments of VB artery stenosis, the 30-day risk of TIA, stroke, or death was 6.4% [6]. In another review of stenting procedures for vertebral or basilar artery stenosis reported up to 2005, the periprocedural risk of stroke or death was 1.6% for proximal vertebral artery stenosis and 13.8% for distal artery stenosis [7]. Other neurological complications, such as vertebral artery dissection, occurred in 2.6% and 6.0% of the cases, respectively, and non-neurological complications, such as inguinal haematoma, in 1.3% and 2.8%. As mentioned above, the complication rates for distal VB stenting do probably not apply to stenting of the distal vertebral artery outside the acute phase of posterior circulation ischaemia. After a mean follow-up of one year, restenosis has been reported to occur in one quarter of the cases of proximal vertebral artery stenting. However, case series are prone to publication bias and the percentages reported may be different in daily clinical practice. In all randomised trials on carotid stenting versus CEA, the 30-day incidence of any stroke or death was 8.2% (126/1492) after stenting [8]. Moreover, a limitation in interpreting data on vertebral artery stenting is the absence of data describing the risk of recurrent stroke in patients with vertebral stenosis on best medical therapy alone.

### Ethical considerations

The study will be conducted according to the principles of the Declaration of Helsinki, as amended in 2000 and clarified in 2004, and in accordance with the Dutch Medical Research Involving Human Subjects Act (WMO). Approval by the local medical ethical review board is required for each participating centre before start of patient inclusion. The patients will be informed about the trial by their treating physician but will whenever possible be asked for consent by a physician not involved in their treatment. Patients should reach a decision about participation within 180 days after the last vertebrobasilar symptom.

The trial compares two existing forms of treatment currently used in many hospitals worldwide. The investigators anticipate that some patients may be harmed inadvertently as a result of either the stenting procedure or the decision to refrain from invasive treatment. The determination of the rate of these adverse outcome events is in fact the major aim of the trial. In the majority of patients with a recently symptomatic carotid stenosis of 50% or greater, CEA reduces the long-term risk of stroke despite the risks of the intervention [5,14] but at present it is unknown whether this also applies to stenting of vertebral artery stenosis. The trial protocol does not subject patients to hazards that would not have been encountered if they had received the trial treatments outside the context of the trial in routine clinical practice, except for the very small chance of a complication of CTA performed one year after start of treatment, such as an allergic reaction or contrast nephropathy. Individual investigators and hospitals are required to take responsibility for the occurrence of any adverse events in the same way as they would do if the treatments were performed outside the trial.

The sponsor/investigator has a liability insurance which is in accordance with article 7, subsection 6 of the WMO.

The sponsor (also) has an insurance which is in accordance with the legal requirements in the Netherlands (Article 7 WMO and the Measure regarding Compulsory Insurance for Clinical Research in Humans of 23 June 2003). This insurance provides coverage for damage to research subjects through injury or death caused by the study.

### Adverse event reporting

An *adverse event *is any unfavourable and unintended sign, symptom, or disease occurring during the follow-up period of the study. Adverse events occurring after randomisation will be recorded on the adverse event page of the CRF.

A *serious adverse event *is defined as any adverse event that results in:

1. death;

2. a life-threatening condition;

3. inpatient hospitalisation or prolongation of existing hospitalisation;

4. persistent or significant disability/incapacity.

An *important medical event *that may not result in one of the above conditions may be considered a serious adverse event when, based upon medical judgement, it may jeopardise the patient and may require medical or surgical intervention to prevent one of the outcomes above. A *reasonably related adverse event *is defined as one that is possibly, probably, or definitely related to the trial treatment.

All serious adverse events occurring within 30 days after stenting (or within 30 days after randomisation in the conservative treatment group) and adverse events that are serious and reasonably related to the trial treatment but occur after the first 30 days require completion of the safety report, which should be sent to the trial co-ordination centre within 5 working days of observation or notification of the event. All serious adverse events not related to trial treatment during follow-up require completion of the safety report at the planned follow-up visits.

Each outcome event will be reported to the Data Monitoring and Safety Committee (DMSC). We propose the DMSC to use the lower limit of the 95% confidence interval of the complication rate as a criterion to advice the Steering Committee to stop the trial. This lower limit should not be higher than 8.2%, the rate reported for carotid artery stenting. Moreover, we will ask the DMSC to perform one interim analysis halfway during the trial, i.e. after one half of the planned patient-years have been accrued. For this interim analysis we propose the simple 3 standard deviation stopping rule proposed by Peto, that essentially advises to stop at p < 0.001 [16]. We consider it highly unlikely, however, that this threshold will be reached in our relatively small feasibility study.

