## Study design

This is a randomised, open, multi-centre clinical trial with masked outcome assessment, comparing the combination of vertebral artery stenting and best medical treatment with best medical treatment alone in patients with a recently symptomatic stenosis of a vertebral artery of at least 50%. A total of 180 patients will be included. Follow-up will continue until one year after inclusion of the last patient.

Endovascular treatment will be performed by an experienced interventional radiologist with a track record of at least 50 interventions in the carotid or vertebral arteries in the last 5 years. The procedure will include percutaneous transluminal angioplasty followed by stenting. The type of stent and the use of a protection device will be left to the discretion of the interventionist. If stent placement is not feasible or deemed contra-indicated, angioplasty without stent placement will be performed. The procedure will be performed under local anaesthesia, with continuous monitoring of heart rhythm and blood pressure. All patients randomised to stenting will receive clopidogrel 75 mg daily starting at least five days before the procedure and continued for 30 days after the procedure. Patients not on clopidogrel the day before the procedure should be loaded with 300 mg clopidogrel at least six hours before stenting. Best medical treatment will be left to the discretion of the neurologist, but should include rigorous control of vascular risk factors, the use of antiplatelet agents, and the use of a statin.

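### The 5-working-day report of all serious adverse events starts at stenting in one arm and at randomisation in the other, so the wait before stenting has no expedited route

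*Protocol article*

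**What the plan says.** The rules are in the protocol article under Adverse event reporting. Two kinds of event need an expedited safety report, with this deadline: "which should be sent to the trial co-ordination centre within 5 working days of observation or notification of the event". The two kinds are:

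- "All serious adverse events occurring within 30 days after stenting (or within 30 days after randomisation in the conservative treatment group");
- "adverse events that are serious and reasonably related to the trial treatment but occur after the first 30 days".

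A slower route covers the rest: "All serious adverse events not related to trial treatment during follow-up require completion of the safety report at the planned follow-up visits". Two further channels have no stated deadline: "Adverse events occurring after randomisation will be recorded on the adverse event page of the CRF", and "Each outcome event will be reported to the Data Monitoring and Safety Committee (DMSC").

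Four other sections set the timing around these rules:

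- Enrolment criteria require that stenting can be done within two weeks of randomisation.
- Study design states: "All patients randomised to stenting will receive clopidogrel 75 mg daily starting at least five days before the procedure". A patient not on the drug the day before gets a 300 mg load at least six hours ahead. The same section adds: "If stent placement is not feasible or deemed contra-indicated, angioplasty without stent placement will be performed".
- Follow-up counts the visits (one day; 1, 6 and 12 months; then yearly) from stenting in the stent arm and from randomisation in the medical arm.
- The Discussion accepts that some patients allocated to stenting may prove to have no significant stenosis at conventional angiography.

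**The concern.** Treatment in the stent arm begins before the procedure, with clopidogrel, but the expedited window opens only at the procedure. The days between allocation and stenting are covered in the medical arm and not in the stent arm. A serious event in that gap that is not an outcome event, such as a non-fatal extracranial bleed on pre-treatment, could reach the co-ordination centre late, while the same event in the medical arm would be due within 5 working days. What is at stake is prompt and equal safety notification in the experimental arm of a trial whose primary aim is safety. No treatment estimate is affected.

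**Working it through.** The plan attaches no figure to this rule, so there is none to reproduce. The first check is to test each clause against one case: a serious, non-outcome event after randomisation and before stenting.

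| Clause | Stent arm, before stenting | Medical arm, same days |
|---|---|---|
| All serious events in the 30-day window, 5 working days | Not met: the event precedes stenting | Met: the clock started at randomisation |
| Related serious events once 30 days have passed, 5 working days | Not met: too early | Not needed |
| Unrelated serious events, at a planned visit | Met if unrelated; first visit is one day after stenting | Not needed |
| Outcome events to the DMSC | Not met: not an outcome event | Not met |
| CRF entry from randomisation | Met, no deadline | Met, no deadline |

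An unrelated event in the gap is therefore reported at a visit. A related one falls under no safety-report clause.

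**Delay for an unrelated event.** Inputs: first visit one day after stenting (Follow-up); wait of up to 14 days (Enrolment criteria); deadline of 5 working days (Adverse event reporting). Assumptions: 5 working days are 7 calendar days (one weekend, no holiday), and the site learns of the event on the day it happens.

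An event *s* days before stenting reaches the visit after *s* + 1 days, so

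extra delay = max(0, *s* + 1 − 7).

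- *s* = 14 (event on the day of randomisation, stenting on day 14): 15 − 7 = 8 days.
- *s* = 10: 11 − 7 = 4 days.
- *s* = 6 or less: 0 days.

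Two weeks is an eligibility condition and not a limit on the actual wait. A later procedure lengthens the largest delay day for day.

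**Exposure in the gap.** With 90 patients in the stent arm (Statistical considerations), all waiting the full 14 days, exposure is 90 × 14 / 365.25 = 3.45 patient-years. The document gives no rate for serious non-outcome events. Purely as an assumption, rates of 5% to 30% per year would give 3.45 × 0.05 = 0.17 to 3.45 × 0.30 = 1.03 events.

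**Patients with no procedure.** There is no stenting date, so the 30-day window never opens and the stenting-based visits have no starting point. Only the close-out visit, set one year after the last patient is randomised, has a date independent of stenting. The group is narrow, because patients who cannot receive a stent have angioplasty and are analysed with the stented patients. It is mainly those without significant stenosis at angiography and those who never reach the procedure.

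**The case against.** The strongest reply is that timing the reports from the procedure is a deliberate choice. The trial asks whether stenting is safe, the visits use the same starting points, and an unrelated event before the stent says little about it. The related-event clause is meant to extend a window in which everything is already expedited, so a sensible site would report a bleed on clopidogrel at once. Events are on the CRF from randomisation, outcome events go to the DMSC, and that committee reviews unblinded data continuously. The article also condenses a fuller protocol that may be clearer.

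Much of this limits the size of the point. The intent for related events is probably as described, and the primary outcome, the precision figures and the stopping criterion are untouched. The 5-day clock runs from observation or notification, so late notification shortens the extra delay, and 8 days is a ceiling for stenting on day 14.

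It does not remove the gap. Clopidogrel exposure before the procedure belongs to the stent strategy. Neither the CRF nor the DMSC route carries a 5-working-day deadline to the co-ordination centre, and the DMSC route covers outcome events only. Nor is this a detail left out for brevity: the article states a specific rule with different starting points by arm, and the gap follows from that rule.

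**Conclusion.** The concern holds, as a minor point. As written, serious non-outcome events between randomisation and stenting have no expedited report in the stent arm but do in the medical arm.

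For unrelated events the extra delay runs from 0 to about 8 days, given stenting by day 14, same-day notification and 5 working days taken as 7 calendar days. For related events before stenting, and for any serious non-outcome event in a patient who has no procedure, the text sets no expedited deadline. Few events are likely to be affected, but their number cannot be derived from the document. No estimate is biased, because events are recorded from randomisation in both arms.

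**What to change.** Reword the reporting sentence so that the 5-working-day report is required for:

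- all serious adverse events from randomisation until 30 days after the endovascular procedure;
- in the medical arm, and in patients allocated to stenting who have no procedure, all serious adverse events until 30 days after randomisation;
- reasonably related serious adverse events at any later time.

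The cost is one reworded sentence and a notice to the sites, since recruitment has begun. No new data are needed, and a few extra expedited reports will follow. The stent-arm window becomes longer, up to 14 + 30 = 44 days against 30 for a two-week wait. That is acceptable, because it covers both the wait and the procedure. A patient whose day-14 angiography ends without intervention would have only 30 − 14 = 16 further days if counted as having no procedure. Counting such an angiography as the procedure would avoid this.

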Case series are prone to publication bias and the percentages reported above may be different in daily clinical practice. The combined 30-day incidence of any stroke or death in randomised trials on carotid stenting versus CEA, was 8.2% (126/1492) after stenting [8]. Moreover, the interpretation of outcome results after vertebral stenting is complicated by the lack of data on the risk of recurrent stroke in patients with vertebral stenosis on best medical therapy alone. Most importantly, the only trial that has compared endovascular treatment with medical therapy in a randomised fashion, included just 16 patients [6,9].

In conclusion, stenting of vertebral artery stenosis appears a promising technique for the prevention of recurrent vascular events in the VB territory, but is still without a proven benefit. The procedure may be complicated by disabling stroke and early restenosis. Before widespread application, the procedure should be assessed in a large randomised trial. As a prelude to such a trial, the present study aims to determine the safety and feasibility of stenting for symptomatic vertebral artery stenosis.

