### Outcome assessment

Clinical outcome assessment will be performed by three independent adjudicators on the basis of an anonymised written description of the outcome event and ancillary investigations. This description will be made by the research physician in such a way that the adjudicators will remain masked to the allocated treatment.

The primary outcome measure will be vascular death, non-fatal myocardial infarction, or non-fatal stroke (neurological deficit lasting longer than 24 hours for which no other cause than a stroke can be found) within 30 days after start of the treatment (see Appendix for definitions).

Secondary outcome measures will be vascular death, non-fatal myocardial infarction, or non-fatal stroke during follow-up. Other outcome measures include any stroke in the supply territory of the symptomatic vertebral artery during follow-up and the degree of stenosis of the symptomatic vertebral artery after one year, as assessed with both Duplex ultrasound and CT angiography.

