### Statistical considerations

With 90 patients in the endovascular intervention arm, a complication rate of 7.8% (7 events) would yield a 95% confidence interval from 3.2 to 15.4%. The estimate of 7.8% is comparable to that of 8.2% for carotid stenting [8]. As the number of patients receiving angioplasty without stent placement is expected to be extremely small, these patients will be analysed together with the patients who have received a stent.

Inclusion of a total of 90 patients in the medical arm during three years and one final year of follow up for these patients will provide 225 patient years of follow up. This number of patient years would yield a 95% confidence interval of 4.1 to 11.5% for an annual event rate of 7%.

An additional analysis will be done to compare the incidence of vascular events between the two treatment groups. This analysis will be based on the intention-to-treat principle and reported in terms of the hazard ratio with corresponding 95% confidence intervals calculated with the Cox proportional hazard model.

We consider the precision of the above estimates sufficient for reliable calculation of the sample size of a conclusive randomised clinical trial.

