### Data Monitoring and Safety Committee

The DMSC performs analyses of the unblinded data on a permanent basis and formulates recommendations for the Steering Committee on the continuation of the trial. The Data Monitoring Committee may also offer unsolicited recommendations.

Members of the Data Monitoring Committee are being sought.

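### The 8.2% set as the DMSC stopping threshold does not match its own counts (126/1492 is 8.45%), and the rule does not say which 30-day events are compared with it

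*Protocol article*

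**What the plan says.** All places are in the protocol article.

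- **Adverse event reporting.** Each outcome event goes to the DMSC. The committee is invited to "use the lower limit of the 95% confidence interval of the complication rate as a criterion" for advising the Steering Committee to stop, with the condition "This lower limit should not be higher than 8.2%, the rate reported for carotid artery stenting". A separate halfway interim analysis with a p < 0.001 rule follows.
- **Background** and **Safety and indemnity.** Both give the source of the threshold. The second reads "the 30-day incidence of any stroke or death was 8.2% (126/1492) after stenting"; the first gives the same percentage and counts, "8.2% (126/1492) after stenting".
- **Statistical considerations.** The design assumption for the stenting arm is tied to the same figure: "The estimate of 7.8% is comparable to that of 8.2% for carotid stenting".
- **Outcome assessment.** "The primary outcome measure will be vascular death, non-fatal myocardial infarction, or non-fatal stroke", within 30 days of the start of treatment.
- **Data Monitoring and Safety Committee.** "The DMSC performs analyses of the unblinded data on a permanent basis".

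**The concern.** The 8.2% is a decision figure: it is the number that the lower confidence limit is held against. Three things about it need attention.

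1. The percentage and the counts printed with it disagree, so a DMSC that checks the threshold cannot reproduce it.
2. The benchmark and the trial's 30-day outcome are different composites, and the rule's term, complication rate, is not defined where the rule is stated. If it means the trial outcome, a composite that includes myocardial infarction is held against a limit that excludes it.
3. No look schedule, minimum number of patients or false-stop probability is given for the criterion. A plain 95% lower limit has its nominal 2.5% one-sided meaning for one look only.

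At stake is whether a crossing, in a trial whose primary aim is safety and feasibility, is read correctly.

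**Working it through.** **Inputs.** Threshold 8.2% and criterion (Adverse event reporting); counts 126/1492 for any stroke or death (Background; Safety and indemnity); 90 stented patients and 7 events (Statistical considerations); 30-day outcome (Outcome assessment).

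**Step 1: which interval the plan uses.** The Clopper-Pearson lower limit for x events in n patients is the 2.5% quantile of Beta(x, n − x + 1); the upper limit is the 97.5% quantile of Beta(x + 1, n − x). For 7/90 = 7.8% this gives 3.2% to 15.4%, the plan's own interval. Wilson gives 3.8% to 15.2% and Wald 2.2% to 13.3%. The exact method is therefore used below.

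**Step 2: the threshold.**
- 126/1492 = 0.08445, that is 8.45%.
- 0.082 × 1492 = 122.3 events.
- 126/0.082 = 1537 patients.

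Neither rounding nor truncation of 126/1492 gives 8.2%.

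**Step 3: effect on the boundary.** The smallest number of events whose exact lower limit exceeds the threshold:

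| Stented patients | Threshold 8.2% | Threshold 8.45% |
|---|---|---|
| 30 | 7 | 7 |
| 45 | 9 | 9 |
| 60 | 10 | 11 |
| 90 | 14 | 14 |

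At n = 60 the lower limit for 10 events is 8.29%, which lies between the two thresholds. Over n = 1 to 90 the boundary differs at 17 sample sizes, each time by one event.

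**Step 4: endpoints side by side.**

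| Component | Benchmark | Trial 30-day outcome |
|---|---|---|
| Stroke | any | yes |
| Vascular death | yes (any death) | yes |
| Non-vascular death | yes | no |
| Non-fatal myocardial infarction | no | yes |

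The two differences act in opposite directions, and the documents give no rate for either, so the net shift cannot be calculated.

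**Step 5: repeated looks.** An exact binomial recursion over n = 1 to 90 carries forward the probability of each event count and removes, at each look, the part at or above the boundary for 8.2%. The sum removed is the probability of ever crossing. The 13.8% column uses the article's figure for distal stenosis as an example of a high rate.

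| Looks | True rate 8.2% | True rate 13.8% |
|---|---|---|
| After every patient | 9.8% | 56% |
| After every patient from n = 20 | 7.2% | 54% |
| At 30, 60 and 90 | 3.4% | 43% |
| At 45 and 90 | 2.1% | 38% |
| At 90 only | 1.5% | 36% |

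Of the 9.8%, 5.4 points accrue in the first 20 patients and 2.0 points in the first five; 2 events in 3 patients already cross (lower limit 9.4%). With 8.45% as both threshold and true rate, continuous checking also gives 9.8%, so the arithmetic slip does not drive this result.

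**The case against.** **On the arithmetic.** The cited source is not at hand, and 8.2% may be a weighted pooled rate rather than a simple ratio. That is possible, but the article prints it as the rate for those counts, so the reader needs to be told. It is also true that the slip hardly moves the boundary.

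**On the endpoint.** The rule does not define complication rate, so the mismatch rests on a reading. The reading is the natural one: the preceding sentence concerns outcome events, and Statistical considerations sets the trial's complication rate beside 8.2%. If it is wrong, the stopping statistic is undefined, which needs the same repair.

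**On repeated looks.** The text does not say that the limit is recomputed after each event. That is inferred from per-event reporting together with permanent analysis. No error rate is claimed, the rule is an advisory proposal, any excess is towards caution, and with looks at 45 and 90 the probability stays below 2.5%. All of this stands, so this part is a trade-off to disclose and not an error.

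**Stronger readings that a reader might infer, and that the documents do not support.**
- *That permanent monitoring contradicts the single interim analysis.* The interim analysis is introduced as a further item with its own p < 0.001 rule, and the two can run together.
- *That this is the only harm boundary.* The p < 0.001 rule sits in the same paragraph and is not restricted to benefit.
- *That the wrong percentage or the endpoint mismatch causes the inflated false-stop probability.* Step 5 shows that it comes from repeated looks alone.

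**Conclusion.** The 8.2% threshold contradicts the counts printed with it in two sections, and the rule leaves open which composite is held against it. Both should be corrected because this figure guides a decision. The numerical effect of the first is small: one event at 17 of 90 sample sizes and none at 90. The size of the second is unknown, since the documents give no rates for myocardial infarction or non-vascular death. The documents do not show whether the percentage, the numerator or the denominator is wrong.

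The repeated-look result is conditional. If the unadjusted limit is checked continuously, the false-stop probability at a true 8.2% is about 10%, or about 7% if checking starts at 20 patients; with looks at 45 and 90 only it is about 2%. These figures assume exact limits, 90 stented patients and complete 30-day outcomes at each look. They do not show that the rule fails a stated error rate, because none is stated.

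**What to change.** 1. Check the cited source. State one consistent count and rate, or say that 8.2% is a pooled estimate that the raw counts do not reproduce, in Background, Statistical considerations, Safety and indemnity, and Adverse event reporting. Carry the verified figure into the rule. This costs a source check.
2. Define complication rate in the rule as any stroke or any death within 30 days, so that it matches the benchmark. Keep reporting myocardial infarction to the DMSC alongside. This has a price: infarctions no longer count towards this numerical criterion, so the committee has to weigh them separately. Non-vascular deaths within 30 days must be available for the count.
3. State the false-stop probability with the rule: about 10% at a true 8.2% under continuous checking, about 7% from 20 patients, about 2% with looks at 45 and 90. Leave the schedule to the DMSC, because fewer looks also lower the chance of detecting harm: at a true 13.8% it falls from 56% under continuous checking to 43% with looks at 30, 60 and 90, a schedule that still has a 3.4% false-stop probability.

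In all, this is a paragraph in the protocol and the DMSC's working rules; the sample size and conduct of the trial do not change.

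### The 3 standard deviation interim rule is glossed as essentially p < 0.001, but 3 SD is p = 0.0027 two-sided (0.00135 one-sided), and the protocol does not say which form governs

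*Protocol article*

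**What the plan says.** The interim rule stands in the protocol article under Adverse event reporting. The DMSC is to be asked to "perform one interim analysis halfway during the trial, i.e. after one half of the planned patient-years have been accrued". The boundary proposed for it is the "simple 3 standard deviation stopping rule", with the explanation "that essentially advises to stop at p < 0.001". The authors then add: "We consider it highly unlikely, however, that this threshold will be reached in our relatively small feasibility study". That sentence speaks of one threshold, so the standard deviation form and the p-value form are treated as a single boundary.

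The interim text gives no sidedness for the p-value. The only between-group comparison described elsewhere is under Statistical considerations, where the incidence of vascular events is to be "reported in terms of the hazard ratio with corresponding 95% confidence intervals calculated with the Cox proportional hazard model".

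**The concern.** A stopping boundary is a cut-off, so its Z form and its p form should mark the same point. Here they do not, on either sidedness. The stated p-value is stricter than the named rule, and between the two lies a band of results for which the sentence supports either piece of advice. A committee that meets such a result would have to settle the meaning after seeing unblinded data, which is what a prespecified boundary is meant to prevent. The DMSC had not yet been formed when the article was written (its members were still being sought), and this is the only interim between-arm boundary that the article offers it.

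**Working it through.** **Inputs.** From Adverse event reporting: 3 standard deviations; p < 0.001; one look at half of the planned patient-years. Sidedness is not stated, so both readings are tried. Φ is the standard normal distribution function.

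**1. From 3 SD to p.**
- Two-sided: 2 × (1 − Φ(3)) = 0.00270.
- One-sided: 1 − Φ(3) = 0.00135.

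The article's p < 0.001 is not reproduced either way. The one-sided value rounds to 0.001 but is not below it. The two-sided value is 0.00270 / 0.001 = 2.7 times the stated figure.

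**2. From p = 0.001 to SD.**
- Two-sided: Φ⁻¹(0.9995) = 3.29.
- One-sided: Φ⁻¹(0.999) = 3.09.

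**3. The band of disagreement.**

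| Reading | 3 SD equals | p = 0.001 equals | Forms disagree for |
|---|---|---|---|
| Two-sided | p = 0.0027 | 3.29 SD | Z from 3.00 to 3.29 |
| One-sided | p = 0.00135 | 3.09 SD | Z from 3.00 to 3.09 |

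**4. Can a result fall in the band?** Assume equal exposure in the arms, so that under no difference each event falls in either arm with probability one half. For a split a:b with n = a + b, the normal approximation is Z = (a − b)/√n.
- 15:2: Z = 13/√17 = 3.15, two-sided p = 0.0016. Exact binomial two-sided p = 2 × (1 + 17 + 136)/2¹⁷ = 308/131,072 = 0.0023.
- 17:3: Z = 14/√20 = 3.13, two-sided p = 0.0018. Exact binomial two-sided p = 2 × (1 + 20 + 190 + 1,140)/2²⁰ = 2,702/1,048,576 = 0.0026.

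On a two-sided reading, both splits lie between 0.001 and 0.0027, whether the approximate or the exact p is used. On a one-sided reading the exact values are half as large (0.0012 and 0.0013) and still lie between 0.001 and 0.00135. The approximate Z values, however, exceed 3.09 and so meet both forms.

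The band is not open at every event count. At 22 events, 18:4 gives Z = 14/√22 = 2.98 (neither form met) and 19:3 gives Z = 16/√22 = 3.41 (both met).

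**5. Effect on type I error.** Assume a look at information fraction 0.5 and a final two-sided test at 1.96 without adjustment; the article states neither in these terms. Numerical integration gives an overall two-sided error of 0.0508 with a boundary at 3.00 and 0.0502 with a boundary at 3.29. The difference is 0.0006.

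**The case against.** The strongest reply is that the sentence names one rule, the 3 SD rule, and that its qualifier marks the p-value as an approximate gloss. On that reading 3 SD governs. Sidedness is also unstated: the factor of 2.7 and the band up to 3.29 SD need a two-sided test, whereas one-sided the p-value is 0.00135 and the band ends at 3.09 SD. The rule is a proposal to an advisory committee, in a condensed article, for a trial sized on the precision of single-arm rates. The comparison between arms is an additional analysis. The separate confidence-limit criterion for the complication rate is untouched.

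Most of this stands and limits the weight of the point. It does not make the p-value right. A gloss on a cut-off should agree with it, and nothing in the article says that the p-value yields to the 3 SD form where the two differ.

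A reader might infer that the same interim data could both stop and not stop the trial. The document does not support that: the committee only advises, and it is offered one named rule with an imprecise gloss. Nor does the point extend to the interim test or outcome being left open. Such detail commonly sits in an analysis plan or committee charter, and neither is shown.

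**Conclusion.** The point holds as a minor but certain inconsistency. The stated p-value does not match the named rule under either sidedness, and the document does not resolve the difference. The mismatch itself rests only on the normal distribution. The event splits are illustrations that also assume equal exposure, and whether a split falls in the band depends on the event count, the sidedness and the test used.

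The practical consequence is small. The authors consider crossing very improbable, the rule is advisory, and the choice between the two boundaries barely affects overall error. A reader might take this for a problem of type I error control; the figures do not bear that out. What remains is a stopping boundary that should have a single meaning before unblinded data are examined.

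**What to change.** Reconcile the one sentence under Adverse event reporting, and carry the same wording into any DMSC charter. State a single governing boundary, its sidedness, and a Z and p that agree. Expressed two-sided, the consistent pairs are:
- 3 SD with p of about 0.0027; or
- 3.29 SD with p = 0.001.

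If a one-sided p-value was intended, the pairs are 3 SD with 0.00135, or 3.09 SD with 0.001, and the sentence should say that it is one-sided.

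The document does not show which boundary was meant, so the sponsor must choose, before the interim data are seen. The cost is one sentence, with no effect on sample size, data collection or the main analyses.
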